### Secondary Endpoints:

***STD Prevalence and GUD.***

This will be assessed in both male trial participants and in female RCSS participants.

Prevalent syphilis and STD symptoms (GUD, discharge/dysuria) at baseline will be compared between study arms. At follow up visits 1 and 2, we will determine the period prevalence of STD symptoms and cumulative prevalence of syphilis (the latter based on prevalence because of persistence in seropositivity). In persons free of initial serologic infection at baseline, incident syphilis will be derived, and covariate adjusted rate ratios of incident STD symptom endpoints will be estimated by Poisson regression modeling as described above.

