## Male STDs and STD Symptoms:

These estimates are based on the total populations of HIV- negative men enrolled in the Gates and NIH trials.

*STDs:*

All participants will be tested for HIV and syphilis at all study rounds. For budgetary reasons, additional specimens will be collected for selective STD testing with other funds. (Please see laboratory methods). From prior data the expected infection rates are: syphilis prevalence ~10% and incidence 2.2/100 py. The RR for syphilis in circumcised versus uncircumcised men was 0.71. With 5492 observations per arm, we have >80% power to detect a RR of 0.70 for the effects of circumcision on syphilis prevalence, and >80% to detect a RR = 0.5 in syphilis incidence.

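### The claimed power of more than 80% for a syphilis prevalence ratio of 0.70 is not supported by the protocol's own prevalence, incidence and cumulative endpoint

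*Protocol*

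**What the plan says.** Protocol section 8.3 (Male STDs and STD Symptoms) gives the expected rates from prior data as "syphilis prevalence ~10% and incidence 2.2/100 py". It adds: "The RR for syphilis in circumcised versus uncircumcised men was 0.71". Two power statements follow. The first concerns prevalence: "With 5492 observations per arm, we have >80% power to detect a RR of 0.70 for the effects of circumcision on syphilis prevalence". The second concerns incidence: ">80% to detect a RR = 0.5 in syphilis incidence".

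Section 8.8.3 (STD Prevalence and GUD) sets out the analysis. Arms are compared on prevalent syphilis at baseline. At follow-up visits 1 and 2 the measure is "cumulative prevalence of syphilis (the latter based on prevalence because of persistence in seropositivity"). The same paragraph then adds an incidence measure: "In persons free of initial serologic infection at baseline, incident syphilis will be derived".

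The eligibility criteria in sections 4.1 and 4.2 do not exclude men who are seropositive for syphilis. Scheduled follow-up is at 6, 12 and 24 months.

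**The concern.** A prevalence ratio between circumcised and uncircumcised men in observational data reflects infections acquired over many years of exposure. In the trial, men are circumcised at enrollment and watched for two years. Men already seropositive are balanced between arms by randomization and, on the protocol's premise of persistent seropositivity, remain positive in both. They add the same amount to each arm's cumulative prevalence and pull the ratio towards 1.

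The target of 0.70 matches the prior 0.71 and appears to have been carried over as if circumcision could lower the prevalence that both arms bring into the trial. At stake is how a cumulative prevalence ratio near 0.9 would be read. Described as a comparison with more than 80% power, it would look like evidence of little effect, although a ratio of that size is what a substantial reduction in new infections would produce.

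**Working it through.** **Inputs from the protocol.** Prevalence p0 = 0.10 and incidence λ = 0.022 per person-year (section 8.3); 5,492 observations per arm (section 8.3); two years of follow-up and 7.5–10% crossover (section 8.2); 2,500 men per arm in the NIH trial and about 6,000 HIV-negative men in both trials, so about 3,000 per arm (section 8.2).

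**Assumptions.** The 10% is taken as enrollment prevalence. A two-sided 5% test and equal arms are carried over from the HIV calculation. The power figures make no allowance for loss to follow-up.

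**1. The plan's own figures.** A ratio of 0.70 on 10% is 10% against 7%. With 5,492 per arm, a two-proportion test has 99.99% power; 80% needs only 1,356 per arm. For incidence, 2.2 against 1.1 per 100 person-years with 5,492 person-years per arm gives 99.3% power (Wald test on the log rate ratio). Both claims of more than 80% are arithmetically consistent as comparisons. The question is whether 10% against 7% can arise.

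**2. Lowest reachable prevalence ratio.** With persistent seropositivity and incidence ratio RR,

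P(t) = p0 + (1 − p0)·(1 − exp(−λ·RR·t)).

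Complete protection from day 0 (RR = 0) leaves the circumcision arm at 10%. The control arm (RR = 1) rises:

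| Time | Control prevalence | Lowest ratio |
| --- | --- | --- |
| 6 months | 10.98% | 0.10/0.1098 = 0.91 |
| 12 months | 11.96% | 0.10/0.1196 = 0.84 |
| 24 months | 13.87% | 0.10/0.1387 = 0.72 |

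Reaching 0.70 would take about 2.2 years of complete protection. If 7.5% of the circumcision arm were unprotected, the 24-month value would be (0.075 × 13.87% + 0.925 × 10%)/13.87% = 0.74.

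**3. Less than complete protection, 24 months.**

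| Incidence ratio | Circumcision arm | Prevalence ratio | Power, 2,500/arm | Power, 3,000/arm | Power, 5,492/arm |
| --- | --- | --- | --- | --- | --- |
| 0.5 | 11.96% | 0.86 | 52% | 60% | 85% |
| 0.71 | 12.77% | 0.92 | 21% | 24% | 40% |

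The last column treats the 5,492 observations as independent men. The protocol does not explain that number, and repeat observations of persistent seropositivity in one man are not independent.

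**4. Sensitivity to the 10%.** Complete protection would just reach 0.70 at 24 months if baseline prevalence were about 9.1%, or if incidence were about 2.44 per 100 person-years. If 10% were instead the 24-month control prevalence, baseline would be about 6.0% and the lowest ratio 0.60. A ratio of 0.70 (7% at 24 months) would then need an incidence ratio of about 0.25, a cut of about 75%.

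**5. Incident syphilis in baseline seronegatives.** Seronegative person-years are taken as 90% of the per-arm total. Power uses ln(1/RR)/√(1/E1 + 1/E2) − 1.96, with E1 = 0.022 × person-years and E2 = RR × E1:

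| Total py per arm | 90% | Power, RR 0.5 | Power, RR 0.71 | RR detectable at 80% |
| --- | --- | --- | --- | --- |
| 3,932 (NIH, section 8.2) | 3,539 | 94% | 49% | 0.59 |
| 5,188 (both trials, section 8.2) | 4,669 | 98% | 61% | 0.64 |
| 5,492 (if person-years) | 4,943 | 99% | 63% | 0.65 |

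**The case against.** The strongest reply is that the plan already holds the right measure. Incident syphilis in men free of serologic infection at baseline is derived in section 8.8.3 and separately powered in section 8.3, and that power statement survives the check. Cumulative prevalence is only to be determined; it is not ranked above incidence, and no test is attached to it in that sentence. All of this stands, and it confines the defect to one power clause and the role given to cumulative prevalence.

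Two stronger readings are tempting, and the protocol does not support either.

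- A reader might infer that a ratio of 0.70 is impossible within two years. At 24 months the gap is only 0.72 against 0.70. It rests on an approximate figure from prior data that is not labelled as enrollment prevalence, and a baseline near 9.1% closes it. What holds is that 0.70 needs complete or very large protection at 24 months, and that it is well out of reach at 6 and 12 months if baseline is about 10%.
- A reader might infer that the plan would answer the secondary objective on STDs wrongly. That would require ignoring the incidence result, which has 94–99% power for a halving of new infections. The objective also covers more than syphilis in men.

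A further reply is that seropositivity may be lost after treatment. The protocol does not quantify this, and its own premise is persistence.

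**Conclusion.** The claim of more than 80% power for a prevalence ratio of 0.70 is wrong as written. It describes 10% against 7%, and 7% lies below the level that both arms would carry from enrollment. On the protocol's figures the attainable ratio is bounded below by about 0.91, 0.84 and 0.72 at 6, 12 and 24 months. Incidence ratios of 0.5 and 0.71 correspond to 24-month prevalence ratios of about 0.86 and 0.92, with about 52% and 21% power at 2,500 men per arm.

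This rests on persistent seropositivity, on seropositive men being enrolled, and on 10% being roughly the enrollment prevalence. The last matters most for the 24-month bound. If 10% is the 24-month control figure, the target is reachable in principle but only with about a 75% reduction in incidence, far more than the prior 0.71 suggests. The incidence analysis and its power for a ratio of 0.5 are sound.

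**What to change.** - Section 8.3: delete the prevalence power clause, or restate it for the cumulative prevalence ratio that a given incidence ratio would produce at a named visit.
- Section 8.8.3: base the between-arm efficacy conclusion for syphilis on the incident-syphilis rate ratio in men seronegative at baseline, and report cumulative prevalence by arm descriptively.
- Section 8.3: state the incidence ratio detectable with 80% power as about 0.60 to 0.65, and name the person-years used (90% of 3,932, 5,188 or 5,492 per arm, the last only if the 5,492 observations are person-years).

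The cost is wording only: no new data, visits or tests. The downside is a less favourable power statement for syphilis. At the prior ratio of 0.71 the incidence analysis has only about 49–63% power, and the text should say so.

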***Behavioral change (disinhibition).***

This will be assessed in both male trial participants and in female RCSS participants.

To assess possible behavioral disinhibition we will determine the frequency and changes in reported frequency of risk behaviors (e.g., number, type of partners, condom use, alcohol use) by study Arm, at enrollment and at each follow up. Data will be displayed graphically for each follow up visit. We will estimate the adjusted odds ratios of risk behaviors in the intervention versus the control arms using multivariate logistic regression for each survey visit. We will assess intra-individual changes in risk behaviors as follows. For continuous variables (e.g., number of partners), the intra‑individual change in risk behaviors from enrollment will be determined, and the mean within‑individual behavioral change between study arms will be assessed using repeated measures ANOVA or paired t tests. For dichotomous variables, we will assess the change in risk behavior over time, and estimate adjusted odds ratios of risk behavioral change between study arms by logistic multivariate regression. For categorical behavioral outcomes (e.g., non use of condoms, inconsistent and consistent use) we will use multivariate polychotomous logistic regression. In addition, we will have data from ongoing cohort surveillance to measure behavioral trends among non-participants, and we will determine behavioral change in the non-trial population in order to assess general trends, and to compare such non-trial associated behaviors with those reported by participants in both arms. A composite riskscore will be developed on the basis of these analyses.

The relevance of changes in risk behaviors with respect to HIV incidence will be determined from prior Rakai studies of risk factors for HIV acquisition and from epidemiologic data generated by the circumcision trial. The behaviors specified above have been shown to be associated with a risk (rate ratio) ~ 2.0 or more in our observational analyses. We will estimate the effect on HIV incidence by study arm, of observed behavioral disinhibition (should it occur), using stratified analyses and multivariate analyses and stochastic modeling.

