## Study Designs

We have conducted two complementary individually randomized, unblinded, two armed trials to assess the efficacy of circumcision for prevention of HIV and STD acquisition in men and women in rural communities of Rakai District, Ugandan. The two trials and study populations are summarized in Table 1 and are as follows:

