**Stopping rules:The following stopping rules are suggested:**

***Efficacy Male HIV Acquisition.*** We proposed an interim analysis at 40 months. This was to include men enrolled in both the NIH and Gates trials. If HIV incidence in one arm significantly exceeds that of the other arm, it was proposed that the trial be discontinued following DSMB review and discussion with the Gates Foundation. We suggested that formal statistical monitoring methods such as the Lan-DeMets group sequential approach 118 with an O’Brien-Fleming type spending function. These methods minimize the chance of inappropriately terminating the trial in its early stages. If interim analyses suggest equivalence of HIV incidence in the two arms, conditional power methods will be used to estimate the chance that further data accumulation will result in significant differences. If the probability is low, consideration will be given to stopping the trial.

Please note, the female acquisition end point cannot be determined prior to the completion of the trial

***Behavioral changes, STDs, and disinhibition.*** It is possible that, despite intensive health education, circumcision may lead to false expectations of protection, engendering increased risk behaviors. If there is evidence of increased risk behaviors we would intensify health education efforts. However, if such improved education is unsuccessful, we suggest establishing stopping rules using the following possible measures of disinhibition in the intervention versus the control arm: a) a significant decline in the frequency or consistency of condomuse, b) a significant increase in the number of extramarital partners, c) a significant increase in use of alcohol with sex, d) a significant increase in HIV incidence or selected STDs which are markers for risk behaviors (e.g., incident syphilis).

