**Condom Promotion:**

Condoms are provided free to all enrolled men who are advised to practice consistent use, and to obtain re-supplies from community depots maintained by the Project. Circumcised men are advised to only resume intercourse after certified wound healing and to practice consistent condom use. Current condom use has increased from 9.9% in 1995 to > 30% in 2001. Use with extramarital partners was 30.8% in 1995 and is currently over 60%. Thus, the Rakai Health sciences Program has markedly increased condom use by the community-based education and distribution program. However, despite repeated intensive Rakai Health sciences Program condom promotion via community meetings, counseling, and community distribution of supplies, consistent condom use remains low (~ 8 % in 2001), hence HIV incidence is stable at around 1.4/100py, and there is a need for innovative prevention interventions.

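### One of the two tests offered for comparing change in number of partners between arms, the paired t test, cannot make that comparison, and the protocol gives no rule for choosing

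*Protocol*

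**What the plan says.** Section 1.3 of the protocol describes "individually randomized, unblinded, two armed trials". No section matches men across arms. Behavioral disinhibition is a secondary objective (section 2.2).

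Section 8.8.3, under Behavioral change (disinhibition), assigns methods by type of outcome:

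- Risk behaviors at each visit: the trial will "estimate the adjusted odds ratios of risk behaviors in the intervention versus the control arms using multivariate logistic regression for each survey visit".
- Change in outcomes introduced by "For continuous variables (e.g., number of partners": the change from enrollment is found for each man, and the mean within-individual "behavioral change between study arms will be assessed using repeated measures ANOVA or paired t tests".
- Change in dichotomous behaviors: the trial will "estimate adjusted odds ratios of risk behavioral change between study arms by logistic multivariate regression".
- Categorical behaviors such as condom use: polychotomous logistic regression.
- Background trend: "we will determine behavioral change in the non-trial population in order to assess general trends".

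Section 8.9 (Stopping rules) lists possible measures of disinhibition in the intervention arm against the control arm. One is "a significant increase in the number of extramarital partners". It names no test.

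**The concern.** The sentence on continuous outcomes states a between-arm comparison and then offers two tests joined by a plain alternative. One of them does not address the comparison. An analyst could follow the protocol to the letter, run paired t tests, and never test whether change differs between arms. This is a stated method that does not fit its stated purpose, so it is more than detail left for later.

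It matters most for number of partners. That is the protocol's own example of a continuous behavior, and this is the only sentence that gives a method for its change. Behavior in this population also moves over calendar time. Section 10.1 (Condom Promotion) reports that "Current condom use has increased from 9.9% in 1995 to > 30% in 2001". That figure concerns condoms and predates the trial, so it shows that trends occur, not what the trend in partners will be. Health education goes to the whole community, so a trend common to both arms is plausible. A test that looks inside one arm cannot separate such a trend from an effect of circumcision.

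**Working it through.** The protocol gives no mean, SD, sample size or power for mean change in number of partners, so there is no figure to reproduce. The only power statement on partners (section 8.5) concerns a proportion, multiple partners rising from 25% to 30%, and does not bear on this sentence.

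**Logic.** Let τ be the trend shared by both arms and δ the added change due to being in the intervention arm. Mean change is τ + δ in the intervention arm and τ in the control arm.

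- Paired t test in the intervention arm: tests τ + δ = 0.
- Two-sample t test on change scores: tests (τ + δ) − τ = δ = 0. With two visits this is the same test as the arm-by-time term of a repeated measures ANOVA.

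The two hypotheses agree only when τ = 0.

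**Illustration.** Assumed, not from the protocol: normally distributed change with SD 1, shifts of 0.1 SD, two-sided 5% level, and 500 or 2,500 men per arm. (Section 8.2 plans 2,500 per arm for the NIH trial; 500 stands for a smaller group.) Hand approximations are set beside a simulation of 2,000 runs.

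*Case A: both arms rise by 0.1 SD, no arm effect (τ = 0.1, δ = 0).*

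- Paired test, 500 men: SE = 1/√500 = 0.0447; 0.1/0.0447 = 2.24; Φ(2.24 − 1.96) = Φ(0.28) ≈ 0.61. Simulated: 61%.
- Paired test, 2,500 men: SE = 1/√2500 = 0.02; 0.1/0.02 = 5; Φ(5 − 1.96) = Φ(3.04) ≈ 0.999. Simulated: 99.8%.
- Two-sample test: true difference 0, so 5% is expected. Simulated: 4.9% (500 per arm) and 4.8% (2,500 per arm).

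*Case B: control falls by 0.1 SD, intervention unchanged (τ = −0.1, δ = 0.1).*

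- Paired test in the intervention arm: τ + δ = 0, so 5% is expected. Simulated: 4.8% at both sizes.
- Two-sample test, 500 per arm: SE = √(2/500) = 0.0632; 0.1/0.0632 = 1.58; Φ(1.58 − 1.96) = Φ(−0.38) ≈ 0.35. Simulated: 33%.
- Two-sample test, 2,500 per arm: SE = √(2/2500) = 0.0283; 0.1/0.0283 = 3.54; Φ(3.54 − 1.96) = Φ(1.58) ≈ 0.94. Simulated: 94%.

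Case A is a shared trend read as disinhibition. Case B is a real arm difference that the paired test cannot see. In both, the larger sample does not help the paired test; in Case A it makes the misreading more certain.

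**The case against.** The strongest reply is that the plan is sounder than this one phrase. Repeated measures ANOVA is named first and makes the right comparison through arm-by-time. The comparison itself is worded correctly, as change between arms. The logistic models at each visit, the odds ratios of change for dichotomous behaviors and the polychotomous model can all carry an arm contrast, and the partner target in section 8.5 is dichotomous and falls under them. All of this stands, and it limits the point to one option for one class of secondary outcome. The trend data from non-participants help less: the men concerned declined enrollment, so they cannot replace the randomized control.

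Four stronger readings are tempting, and the protocol does not support them.

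- A reader might infer that paired t tests are the planned method. They are one of two alternatives, and the harm arises only if they are chosen.
- A reader might infer that an arm difference will be declared when one arm's test is significant and the other's is not, and so expect a false difference about half the time. With two independent tests of power p, disagreement has probability 2p(1 − p): 50% at p = 0.5 and 32% at p = 0.2 or 0.8. But the protocol states no such rule, and p is assumed. In Case A, disagreement was 48% with 500 per arm and under 1% with 2,500, where both tests nearly always reject.
- A reader might infer that stopping could rest on the paired test. Section 8.9 only suggests these measures, after improved education has failed, and already frames them as intervention against control.
- A reader might cite the advice to abstain until wound healing as a source of common trend. It applies to circumcised men for a short time, so during the comparison it falls mainly on one arm.

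That number of partners is a skewed count is a separate matter. It does not make count regression the only acceptable choice.

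**Conclusion.** The sentence is wrong as written, and the matter is minor. One of the two tests named for the between-arm comparison of change in continuous behaviors has no between-arm contrast, and nothing in the protocol says which test will be used. If the paired t test is chosen, a shared trend may pass for disinhibition or conceal it. If repeated measures ANOVA is chosen and the arm-by-time term is read, no harm follows.

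The conclusion about the test needs only the independence of the arms, which section 1.3 establishes. The size of any distortion cannot be estimated, because the mean and SD of change are not given. The percentages above rest on an assumed SD of 1 and assumed shifts of 0.1 SD, and they show the mechanism only. A statistical analysis plan, if one exists, was not available; it might settle the choice of test, but the protocol sentence would still need correcting.

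**What to change.** In section 8.8.3, delete the paired t test as a method for the between-arm comparison and name the arm contrast. Suggested wording:

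> For continuous variables, change from enrollment will be compared between arms with a repeated measures model; the arm effect is the arm-by-time term. Change within each arm will be reported descriptively only.

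A two-sample or ANCOVA comparison of change, or a count regression with an arm term, would serve equally well; one should be named. The change costs one or two sentences and needs no new data, visits or sample size. It should be made before behavioral data are examined by arm.

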### Randomization

- Johns Hopkins generated a list of randomized numbers in blocks of 20 to insure comparability of men randomized to intervention and control arms, within cohort communities or groups of “walk in” participants”.

- A random assignment sheet was placed in an opaque sealed envelope generated by Rakai health sciences Program Data management using a computerized list provided by JHU, and was retained securely by the Circumcision Data Management Team.

- After enrollment and consent, men were asked to select an envelope from the block of 20 envelopes being used at that time. The envelope contained the assignment sheet showing the randomization number and random assignment to treatment or control arm. The Enrollment Team then affixed the label with the individual’s study ID number to the sheet. (Form 18). - The assignment sheet with the study ID# labeled was entered into a data base to record study arm allocation.

- The list of random allocation numbers linked to participants was retained in locked files, and in password protected computers.

- All randomization envelopes were logged out and in daily. A data base monitored used and unused allocation numbers, and tracked disposition of all envelopes.

- Men were randomized at the enrollment visit. If participants change their minds and withdrew, or at a subsequent preoperative visit, the surgeon determined that circumcision was contraindicated for medical reasons, the men were still considered enrolled and randomized. - Men were offered tetanus toxoid immunization.

-After randomization, men completed a consent comprehension test to ensure that they understand the trial and to correct any misunderstandings.

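### For continuous risk behaviours, one of the two methods offered for comparing arms, the paired t test, contains no arm contrast

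*Protocol*

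**What the plan says.** Section 8.8.3 (Secondary Endpoints, behavioural change) sets out how disinhibition will be analysed. The sentence at issue opens with "For continuous variables (e.g., number of partners" as its example. It defines each man's change from enrollment and then says that "the mean within‑individual behavioral change" "between study arms will be assessed using repeated measures ANOVA or paired t tests".

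The same paragraph handles the other variable types differently. It plans "adjusted odds ratios of risk behaviors in the intervention versus the control arms using multivariate logistic regression for each survey visit". For change in dichotomous behaviours it will "estimate adjusted odds ratios of risk behavioral change between study arms by logistic multivariate regression". Categorical outcomes go to polychotomous logistic regression.

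Two statements elsewhere fix the structure of the data. Section 1.3 (Study Designs) describes "individually randomized, unblinded, two armed trials". The Randomization section (4.3.4) says "Johns Hopkins generated a list of randomized numbers in blocks of 20 to insure comparability of men randomized to intervention and control arms". Neither matches an intervention man to a control man.

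**The concern.** The stated question is whether mean change differs between two randomized arms. A paired t test asks whether mean change differs from zero in a single group. It can be run in each arm or on all men together, but in neither form does it estimate a difference between arms.

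The distinction matters most when both arms drift together. The protocol predicts no such drift, but it gives reasons to think one plausible: health education and condoms go to all residents, community condom use rose from 9.9% in 1995 to over 30% in 2001 (section 10.1), and section 8.8.3 itself plans to measure general trends in non-participants. Disinhibition is a named secondary objective (section 2.2), so a test that responds to the common trend would bear on a question that the trial means to answer.

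**Working it through.** The protocol gives no sample size, alpha, standard deviation or effect size for the mean-change analysis, so there is no stated figure to reproduce. The check is of what each test responds to.

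**What each test targets.** Let μ_I and μ_C be the true mean changes in the intervention and control arms.

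- Paired t test within one arm: targets μ_I or μ_C alone.
- Paired t test on both arms pooled (equal arms): targets (μ_I + μ_C)/2.
- Two-sample test of change scores: targets μ_I − μ_C. With two time points it is equivalent to the arm-by-time test of repeated measures ANOVA.

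Only the last is zero when, and only when, the arms change equally.

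**Assumptions for illustration (not in the protocol for this analysis).** Two-sided alpha 0.05; SD of change = 1 in each arm; normal approximation; n = 2,125 per arm (2,500 × 0.85, the NIH-trial figures in section 8.2) or n = 500 per arm (half of the roughly 1,000 HIV-negative men declining VCT).

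**Formula.** Rejection probability = Φ(m/se − 1.96) + Φ(−m/se − 1.96), where m is the quantity targeted and se is 1/√n within an arm, 1/√(2n) pooled and √(2/n) for two samples. With p_I and p_C the within-arm probabilities, the chance that exactly one arm is significant is p_I(1 − p_C) + p_C(1 − p_I).

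For n = 2,125 and a change of 0.05 SD: 1/√2,125 = 0.0217 and 0.05/0.0217 = 2.305, so the within-arm probability is Φ(0.345) = 0.635. Exactly one arm significant: 2 × 0.635 × 0.365 = 0.464.

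| n per arm | Mean change (intervention, control) | Paired, each arm | Exactly one arm significant | Paired, pooled | Two-sample |
|---|---|---|---|---|---|
| 2,125 | +0.05, +0.05 | 64% | 46% | 90% | 5% |
| 2,125 | +0.05, −0.05 | 64% | 46% | 5% | 90% |
| 500 | +0.05, +0.05 | 20% | 32% | 35% | 5% |
| 500 | +0.05, −0.05 | 20% | 32% | 5% | 35% |

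With no arm difference, the pooled paired test rejects in 90% of trials (n = 2,125). With a true difference of 0.10 SD it rejects in 5%, no more than chance. The pattern of exactly one significant arm is equally frequent in both situations, so it carries no information about the contrast. The two-sample test behaves as it should in every row.

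**Without a sample size.** If both arms change equally and each within-arm test has power p, exactly one is significant with probability 2p(1 − p): 2 × 0.5 × 0.5 = 50% at p = 0.5, and 2 × 0.8 × 0.2 = 32% at p = 0.8. The 50% is the maximum. With a common change of 0.10 SD and 2,125 men per arm, nearly every within-arm test is significant (99.6%) and the figure falls to 0.8%.

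**The case against.** Repeated measures ANOVA is the option named first, and it can test the arm difference. The sentence also compresses two tasks, describing change within men and comparing it between arms; a paired t test is the usual tool for the former. On that reading this is a slip of terminology. Much of this stands: the intended question is plainly between arms, and a competent analyst would probably choose correctly. But the wording attaches both methods to the between-arm comparison and joins them with *or*, so the paired t test alone would comply with the plan.

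A reader might go further and infer that the paired t test is the planned method, or that the trial will declare a difference when one arm is significant and the other is not. The documents support neither. The paired test is one of two options, and no per-arm decision rule is stated; the 50% and 32% figures show what would follow if such a rule were used, at assumed power.

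A reader might also infer that a stopping decision hangs on this test, because section 8.9 lists "a significant increase in the number of extramarital partners" among possible measures. That section only suggests establishing rules, frames them as intervention versus control, and names no test.

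Finally, the disinhibition objective does not rest on this sentence alone. The behaviours powered in section 8.5, including multiple partners (25% versus 30%), are proportions, and the logistic models compare those between arms.

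**Conclusion.** The point holds in a limited form. For continuous behaviours, one of the two methods offered cannot answer the stated question, and the other can only through a term the protocol leaves unnamed. That the paired t test lacks an arm contrast follows from the independence of the arms and needs no numerical assumption. How often it would mislead depends on the common trend, the spread of change scores and the way results were combined, none of which the protocol gives; the percentages above are illustrations.

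The scope is continuous behaviours in one secondary endpoint. It would be wrong to conclude that the disinhibition analysis as a whole is invalid: the per-visit logistic, dichotomous-change and polychotomous analyses are not affected. The correction is worth making because following that option would give a wrong answer and the remedy costs almost nothing.

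**What to change.** In section 8.8.3, delete paired t tests as a method for comparing arms, or keep them explicitly as a description of change within an arm. Then name the contrast that will be tested and reported, choosing one of:

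- the follow-up value compared between arms with adjustment for the enrollment value (preferred);
- the arm-by-visit term of the repeated measures model;
- a two-sample comparison of change scores.

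Any of the three repairs the error; the preference for baseline adjustment is a refinement. The cost is a sentence of protocol or SAP wording. The enrollment and follow-up behaviours are already collected, so no new data, visits or sample size are needed.
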